### Participant timeline {13}

The participant timeline is shown in Fig. 3.

**Fig. 3 Fig3:**
[figure not shown]
Participant timeline

### Sample size {14}

Sample size calculation is based on our primary outcome, a priori defined to be the between-group difference at 12 weeks on the PSYRATS-AH total score. We consider a clinically relevant between-group difference on this scale to be 3.8 (with a pooled SD of 11.0; based on calculations from the AVATAR trial [23]). With a two-sided alpha of 0.05 and a power of 80%, this will require 133 participants to be randomised to each of the two interventions (i.e. 266 participants in total).

### Recruitment {15}

The research team collaborates with clinicians from in- and outpatient facilities in the Capital Region of Denmark, the North Denmark Region, and the Region of Southern Denmark. Patients meeting the listed inclusion criteria will be approached by the clinicians who initially inform the patients about the CHALLENGE trial. When patients are interested in participation, clinicians refer them to the trial. Additionally, patients can self-refer to the trial.

#### Concealment mechanism {16b}

At each site, personnel who are *not* blind to the treatment arm are responsible for the randomisation process. When a participant has been recruited for the study and baseline assessment has been conducted, the assessor informs the person responsible for conducting the randomisation process via e-mail.

Randomisation is centralised and computerised with a concealed randomisation. Block size will be unknown to the investigators and clinicians. The randomised intervention allocation is concealed until the statistical analyses of the resulting data have been completed and conclusions have been drawn.

#### Implementation {16c}

The members of the research unit of the Copenhagen Research Center for Mental Health (CORE) will be responsible for the implementation of the trial in the Capitol Region of Denmark, whilst the members of the CHALLENGE trial in the North Denmark Region (Aalborg, DK) and Region Southern Denmark (Esbjerg, DK) will be responsible for the implementation locally.

### Assignment of interventions: blinding

#### Who will be blinded {17a}

Assessors conducting the outcome evaluation are blinded. Due to the nature of the intervention, participants, therapists performing the VRT and clinicians in charge of supportive counselling or standard care are not masked.

Most assessors of the CHALLENGE trial have offices at a different location than the therapists. In one of the sites (Capital Region of Denmark), assessors’ offices are located in the same building as the therapists, but assessors and patients arriving for assessment use a different entrance to prevent unblinding.

#### Procedure for unblinding if needed {17b}

For the follow-up interviews, patients are instructed in advance not to reveal what type of treatment was received. If unblinding occurs, another assessor, blind to treatment allocation, will conduct the subsequent assessments. When possible, another assessor will perform the rating based on a video recording of the assessment (where unblinding occurred, but with this part of the video left out) in order for the patient not to have to sit through the assessment twice within a short time period.

### Data collection and management

#### Plans for assessment and collection of outcomes {18a}

Assessment will be conducted at baseline and at 12 and 24 weeks post-baseline. The PSYRATS-AH (the primary outcome of the study) has been shown to have high inter-rater reliability (ranging from 0.79 to 1.00) as well as good validity [28, 47]. Assessments will be conducted by trained psychologists at each treatment site. The main author of this article ([name]) is a psychologist with a specialisation in psychiatry. [name] is responsible for the training of all assessors. In the training process, supervised co-interviews are conducted. During the data collection phase, videotaped assessments are distributed among assessors for monthly consensus meetings. A random selection of video-taped interviews is scored individually by all assessors. ICC scores will subsequently be calculated and reported.

In case a participant meets the discontinuation or exclusion criteria during the study, or leave the intervention programme prematurely, clinical and functional assessments will still be performed, if possible.

#### Plans to promote participant retention and complete follow-up {18b}

Patients participating in the study will be contacted by telephone before the planned follow-up interviews. Assessors are flexible and can rearrange the scheduled time if needed. Patients who are in an unstable condition can be assessed at home or if hospitalised at the ward at which they are admitted. A taxi can be arranged when needed. If participants are not capable of completing the full assessment battery, the interview is abbreviated, i.e. primary and secondary outcomes are prioritised over other outcome measures.

#### Data management and confidentiality {19} {27}

Data from the patient interviews will be entered directly into the electronic case report form (CRF) using the data entry system REDCap. When necessary, the collection will be done on paper and later entered electronically. REDCap has a complete audit trail on all data transactions, detailed user rights and access control management and thereby complies with Danish legislation (Databeskyttelsesforordningen). Data for each patient is connected to a unique serial number. Only assigned researchers can access REDCap with all the data. Data on paper is stored locally and secured. Research data will be exported from REDCap without personal identifiers.

#### Plans for collection, laboratory evaluation and storage of biological specimens for genetic or molecular analysis in this trial/future uses {33}

None.

## Statistical methods

### Statistical methods for primary and secondary outcomes {20a}

Analysis of outcome will be carried out with the intention-to-treat principles. The planned comparisons between the two groups will be carried out with linear mixed model analyses with repeated measurements and an unstructured covariance matrix for normally distributed outcome measures.

No adjustments will be made for multiple comparisons, as the exploratory outcomes will primarily be used for hypothesis generation; however, interpretations regarding these exploratory analyses will be cautious for this reason.

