#### Intervention description {11a}

*Supportive counselling (comparison group)* is managed by the psychiatric outpatient facility that governs the participant’s treatment. A minimum of seven sessions are delivered encompassing sessions with health professionals providing different types of supportive counselling, i.e. appointments with a nurse, psychiatrist, psychologist, social worker, or different types of interventions, e.g. psychotherapy or group interventions. The counselling offered is expected to be better than standard care (TAU) which often consists of fewer sessions. The type of supportive counselling can be expected to differ from one psychiatric outpatient facility to another which is also the case for patients in the experimental group who receives VRT as an add-on to TAU, in which supportive counselling can still be part of patients’ standard care.

The caseload of clinicians in outpatient facilities will vary—which is also true for clinicians in the experimental condition, since most psychotherapists in the study are primarily employed by outpatient facilities, i.e. they are working part-time in the CHALLENGE trial.

The number and type of interventions received by each patient in both outpatient facilities and (when relevant) inpatient facilities will be registered when participants have terminated their participation in the study enabling conducting of statistical analyses examining the potential between-group differences regarding mental health contacts.

Patients in *the experimental treatment condition* will be offered seven individual sessions of VRT [23] within the first 12 weeks of the study and two booster sessions in the following 12 weeks, all conducted by a skilled therapist (psychologists, doctors or nurses with experience in treating patients suffering from psychosis) (Fig. 1). The therapy rests upon the exposure therapy developed by Leff et al. [23, 26]. The intervention manual of the current trial adds elements of cognitive-behavioural therapy and compassion-focused therapy. As mentioned in the previous section, most therapists are clinicians working in different psychiatric outpatient facilities (employed part-time in the CHALLENGE trial), i.e. their caseload will vary accordingly.

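### The primary model and the sample size make no allowance for clustering by VRT therapist; if outcomes vary between therapists, the standard error is too small and the 80% power is overstated

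*Protocol article*

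**What the plan says.** Statistical methods {20a} states: "The planned comparisons between the two groups will be carried out with linear mixed model analyses with repeated measurements", with an unstructured covariance matrix. It names no therapist, facility or site term. Methods for additional analyses {20b} lists none, so no therapist-adjusted analysis is announced there either.

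Sample size {14} starts from this target: "We consider a clinically relevant between-group difference on this scale to be 3.8 (with a pooled SD of 11.0". With two-sided alpha 0.05 and 80% power it concludes that "this will require 133 participants to be randomised to each of the two interventions". No design effect is mentioned.

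Intervention description {11a} says the VRT sessions are individual and "all conducted by a skilled therapist (psychologists, doctors or nurses with experience in treating patients suffering from psychosis". The therapist's own transformed voice becomes the avatar's, and the therapist switches between speaking as the avatar and as a supportive therapist. On workload, {11a} says that "most therapists are clinicians working in different psychiatric outpatient facilities (employed part-time in the CHALLENGE trial), i.e. their caseload will vary accordingly". All therapists share a fortnightly peer supervision and a monthly supervision.

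On the comparator, {11a} says: "The type of supportive counselling can be expected to differ from one psychiatric outpatient facility to another". It adds that the same applies to VRT participants, who stay with their usual facility. Randomisation {16a} is stratified by site and gender.

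**The concern.** In this therapy the therapist is part of the treatment. Participants seen by the same therapist may therefore have outcomes more alike than participants seen by different ones. An unstructured covariance over visits handles repeated measurements on one participant, but not resemblance between participants who share a therapist.

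If that resemblance exists and is left out, the variance of the VRT arm mean is understated. The confidence interval for the 12-week difference in PSYRATS-AH total is then too narrow, and the trial has less power than stated. This matters here because the Discussion presents the trial as a rigorous test and as a test of applicability by clinic-based therapists. Generalising to other therapists requires that their variation be in the standard error.

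That therapists are shared is an inference, since the article gives no caseload figure. The inference is strong: without sharing, 133 VRT participants would need about 133 therapists, which sits poorly with one joint supervision scheme.

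**Working it through.** **Inputs from the article.** Difference 3.8, SD 11.0, two-sided alpha 0.05, power 80%, 133 per arm (Sample size {14}).

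**Inputs assumed.** Therapist ICC of 0.01, 0.05 and 0.10, and 8, 15 or 30 therapists, which gives m = 133/8 = 16.6, 133/15 = 8.9 or 133/30 = 4.4 VRT participants each.

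**Step 1: the plan's own figure.** With the normal approximation, n per arm = 2 × (1.96 + 0.8416)² × (11.0/3.8)² = 131.5, so 132. The two-sample t-test gives 132.5, so 133. Power at 133 per arm is 80.4% (normal) or 80.1% (t-test). The figure is reproduced with independent participants and leaves no room for a design effect.

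**Step 2: clustering in the VRT arm only.**

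- Design effect in the VRT arm: DE = 1 + (m − 1) × ICC
- True SE divided by model SE: R = √((1 + DE)/2)
- Actual two-sided type I error of the unclustered test: 2 × (1 − Φ(1.96/R))
- Power with the correct SE: Φ(3.8/(1.349 × R) − 1.96), where 1.349 = 11.0 × √(2/133)

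Example with 15 therapists and ICC 0.05: DE = 1 + 7.87 × 0.05 = 1.393; R = √(2.393/2) = 1.094; type I error = 2 × (1 − Φ(1.79)) = 7.3%; SE = 1.476; power = Φ(3.8/1.476 − 1.96) = 73.1%.

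| Therapists (participants each) | ICC | R | Type I error | Power with correct SE |
|---|---|---|---|---|
| 8 (16.6) | 0.01 | 1.04 | 5.9% | 77.4% |
| 8 (16.6) | 0.05 | 1.18 | 9.7% | 66.6% |
| 8 (16.6) | 0.10 | 1.33 | 14.2% | 56.0% |
| 15 (8.9) | 0.01 | 1.02 | 5.5% | 78.9% |
| 15 (8.9) | 0.05 | 1.09 | 7.3% | 73.1% |
| 15 (8.9) | 0.10 | 1.18 | 9.7% | 66.5% |
| 30 (4.4) | 0.01 | 1.01 | 5.2% | 79.8% |
| 30 (4.4) | 0.05 | 1.04 | 6.0% | 77.1% |
| 30 (4.4) | 0.10 | 1.08 | 7.0% | 74.0% |

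With ICC 0, or one participant per therapist, type I error stays at 5%.

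**Step 3: simulation.** A t-test on 12-week values (not the full repeated-measures model), with 20,000 simulated trials per setting, agrees. At ICC 0.05 type I error is 9.6% with 8 therapists and 7.4% with 15.

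**Step 4: clustering in both arms.** If the control arm is clustered to the same degree in its own separate clusters, the simulation gives 14.6% and 9.7% for those two settings. Facility differences that affect both arms alike would partly cancel in the comparison, so this is not a forecast. It shows only that control-arm clustering cannot be assumed to make the problem smaller.

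**Step 5: size needed.** For 80% power at ICC 0.05 with caseload held fixed, n per arm = (2.8016 × 11.0/3.8)² × (1 + DE) = 65.77 × (1 + DE). That is 143 with 30 therapists, 158 with 15 and 183 with 8.

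**The case against.** **The model description is short and excludes nothing.** It lists no random effects, no adjustment terms and no degrees of freedom, and an analysis plan that is not shown could add a therapist term. This stands: the silence alone is not an error. But the power figure is a stated number, and it holds only for independent participants. The article also describes itself as the full trial protocol and announces no additional analyses.

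**A type I error above 5% is not established.** A reader might infer that the test is already known to be anti-conservative. The documents do not support that, because they give no ICC, number of therapists or caseload. Part-time therapists spread over different facilities also fit a large pool with small caseloads, where the excess is slight. The intervention manual, the supervision and the fidelity ratings may keep therapists alike, though they do not show that the ICC is zero.

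**The null hypothesis matters.** If VRT changes nothing for anyone, individual randomisation keeps the unclustered test at about 5%. Inflation needs an average effect of zero with effects that differ between therapists, and therapists viewed as a sample from a wider population. This is correct and limits the type I error claim. The understated standard error and overstated power remain whenever therapists' results differ and conclusions are meant to reach beyond them.

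**The control arm is not free of clustering.** A reader might infer that only VRT participants are clustered. The article points the other way: control care is run by outpatient facilities, may include group interventions, and is expected to differ between them. A model that treats every control participant as unrelated to all others therefore needs its own check.

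**Conclusion.** The point holds conditionally. The primary model and the sample size, as stated, make no allowance for therapist clustering in a treatment delivered by individual therapists. If the therapist ICC is positive and therapists treat more than one participant, the standard error is too small, by a factor of 1.01 to 1.33 over the assumed range. Type I error is then about 5.2% to 14% and power about 80% to 56%. With 30 therapists and ICC 0.01 the effect is negligible.

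The direction follows from the design. The size rests on assumed ICCs and therapist numbers, equal caseloads, clustering in the VRT arm only and a normal approximation, which is somewhat favourable when therapists are few. The change is worth making because it is cheap and because the stated size has no slack.

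**What to change.** 1. Record the first assigned VRT therapist for each participant in that arm, and analyse by that assignment.
2. Add a random therapist effect in the VRT arm (a partially nested mixed model) with Satterthwaite or Kenward-Roger degrees of freedom. Make it the primary model, or at least a prespecified sensitivity analysis.
3. Include site, already a stratification factor, in the model. Do not take the control arm as unclustered: check clustering by outpatient facility in a sensitivity analysis.
4. Report the therapist ICC with the results, and state beside the sample size that the 80% power assumes no therapist clustering.

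The cost is one model term, a therapist identifier and a facility identifier in the analysis dataset, and a less favourable power statement. No new participants or assessments are needed. The interval may be wider, and with few therapists the between-therapist variance will be imprecisely estimated. If the ICC turns out close to zero, little is lost.

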### Interim analyses {21b}

There will be no interim analyses.

### Methods for additional analyses (e.g. subgroup analyses) {20b}

None.

### Methods in analysis to handle protocol non-adherence and any statistical methods to handle missing data {20c}

Missing data are handled implicitly by the linear mixed models through full information maximum likelihood. Analyses will be conducted according to the intention-to-treat principles, i.e. analysing individuals to their allocated groups regardless of, e.g., protocol non-adherence.

### Plans to give access to the full protocol, participant-level data and statistical code {31c}

The document constitutes the full trial protocol. Following completion of the trial, datasets and statistical code used in this study will be available from the corresponding author on reasonable requests.

### Oversight and monitoring

#### Composition of the coordinating centre and trial steering committee {5d}

The trial will be overseen by a Project Management Group (PMG) and a Trial Steering Committee (TSC). The PMG will comprise the PI of the study, the daily leader of the trial, the principal therapist of the trial and the local trial managers from each of the sites conducting the study. The PMG will have a teleconference approximately every 4–6 weeks during the recruitment period. The PMG will support any decision-making that the trial management team need further advice on.

The TSC will include representatives from (1) Mental Health Services in the Capital Region of Denmark, (2) Mental Health Services in the North and Southern Region of Denmark, (3) the Innovation Fund (the trial sponsor) and (4) Khora (the software development company involved in the study). The TSC will meet bi-annually.

#### Composition of the data monitoring committee, its role and reporting structure {21a}

There is no independent Data Monitoring Committee. The PMG will oversee trial safety and consider trial progress, especially recruitment and retention status and report to the Trial Steering Committee. The PMG can appoint additional members to assist in the process. No representatives from the trial sponsor or the IT company developing the software for the trial take part in data monitoring.

#### Adverse event reporting and harms {22}

The use of virtual reality can cause cybersickness. VR-assisted psychotherapy with patients suffering from psychosis is, however, in general considered to be well-tolerated [20]. Therefore, we do not expect any adverse events to happen. Serious adverse events will, though, be monitored and recorded throughout the study period, as well as complaints about the psychotherapy. The following are considered adverse events: (1) hospital admissions, (2) suicide attempts, (3) any violent incidents necessitating police involvement (whether victim or accused), (4) self-harming behaviour and (5) all deaths. Serious adverse events deemed related to the trial will be reported to the Committee on Health Research Ethics of the Capital Region of Denmark.

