#### Criteria for discontinuing or modifying allocated interventions {11b}

Participants can choose to discontinue treatment at any time. If patients experience deterioration in their mental health status and/or are hospitalised during the treatment phase, the intervention can be modified accordingly, e.g. therapy can be conducted during a hospital stay (when considered relevant and safe) or the therapy can be paused. If deterioration may be a consequence of the intervention, the case is dealt with in supervision and severe cases (e.g. severe self-harm or suicide attempts) are also discussed in the project managing group, with the purpose of deciding if the intervention needs to be terminated.

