#### Exploratory outcomes

Exploratory outcome measures are rated at the cessation of treatment at 12 weeks and at 24 weeks of follow-up and includes the revised Beliefs About Voices Questionnaire [9] (BAVQ-R: Malevolence-, Benevolence-, Omnipotence- subscales [9]); the Voices Acceptance and Action Scale (VAAS) [30]: the VAAS acceptance subscale, and total score; Assertive Responding to Voices (Approve - Voices) [31] with aggressive and submissive responding subscales reported; the Brief Core Schema Scales: Beliefs about self and others [33]; General Self-Efficacy [34]; Emotion Regulation Questionnaire (ERQ) [35]; PSYRATS-DEL [28]; Scale for the Assessment of Positive Symptoms (SAPS) [36]; Scale for the Brief Negative Symptoms Scale (BNSS) [37]; Self-evaluation of Negative Symptoms (SNS) [38]; Calgary depression Scale [39]; WHO Well-being Index, WHO-5 [40]; Client Satisfaction Questionnaire (CSQ) [41]; Childhood Trauma Questionnaire (CTQ) [42]; Social Functioning Scale (SFS) [43]; The Suicidal Ideation Attributes Scale (SIDAS) [44] and Pittsburgh Sleep Quality Index (PSQI) [45]. Simulator Sickness Questionnaire (SSQ) [46] is administered in the experimental condition only.

The primary and secondary measures listed above are considered exploratory measures at 24-week follow-up.

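### The adverse-event definition leaves out milder deterioration that the protocol itself says the intervention may cause, and the simulator-sickness results are not linked to the harms report

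*Protocol article*

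**What the plan says.** All references are to the protocol article.

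- **Adverse event reporting and harms {22}** opens with "The use of virtual reality can cause cybersickness". It calls VR-assisted psychotherapy generally well tolerated in psychosis and concludes: "Therefore, we do not expect any adverse events to happen".
- The same section then states "Serious adverse events will, though, be monitored and recorded throughout the study period, as well as complaints about the psychotherapy".
- It defines the term by a list: "The following are considered adverse events: (1) hospital admissions, (2) suicide attempts, (3) any violent incidents necessitating police involvement (whether victim or accused"), and the list ends with "4) self-harming behaviour and (5) all deaths". The word serious is not defined.
- **Criteria for discontinuing or modifying allocated interventions {11b}** says "If deterioration may be a consequence of the intervention, the case is dealt with in supervision". Severe cases, with severe self-harm and suicide attempts as examples, also go to the project managing group. The section does not say that these cases are recorded as adverse events.
- **Exploratory outcomes** states that the "Simulator Sickness Questionnaire (SSQ) [46] is administered in the experimental condition only". Symptom and suicidality scales, including SAPS, the Calgary scale and SIDAS, are listed there with no restriction to one arm.

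**The concern.** The intervention has patients confront a representation of a hostile voice, so a temporary or lasting worsening of voices or distress is its most plausible harm. The protocol anticipates this in item 11b. Yet the rule for what counts as an adverse event covers such worsening only once it becomes an admission, self-harm, a suicide attempt or another listed event.

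What is at stake is the meaning of a later tolerability statement. In reviewing earlier trials, the article itself sets good tolerability beside an absence of reported adverse events. A similar statement made here from the event count would say nothing about milder worsening. The mixed model compares group means, and a better mean is compatible with some participants getting worse.

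**Working it through.** **The plan's own figure.** The harms section contains no number. The only derived figure in the article is the sample size, which serves here just as a denominator. Inputs from Sample size {14}: difference 3.8, SD 11.0, two-sided alpha 0.05, power 80%.

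- Normal approximation: n = 2 × (1.960 + 0.842)² × (11.0/3.8)², rounded up to 132 per arm.
- t-test version: 132.5, rounded up to 133 per arm, or 266 in total. This reproduces the stated figure.

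**Which harms reach the adverse-event count**

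| Harm named in the protocol | On the list in {22}? | Captured elsewhere? |
|---|---|---|
| Hospitalisation {11b} | Yes | Contact registration {11a} |
| Severe self-harm, suicide attempt {11b} | Yes | Project managing group {11b} |
| Milder deterioration possibly due to the intervention {11b} | No | Supervision {11b}; outcome scales; a complaint, if one is made |
| Cybersickness {22} | No | Simulator Sickness Questionnaire, VRT arm only |

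The third and fourth rows are the gap. The third has no stated route into the harms record. The fourth is measured but not linked to it.

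**The expectation of no events.** It follows a sentence naming a known effect of VR, and it does not fit item 11b, which provides for deterioration caused by the therapy. General tolerability of VR does not imply that none of the five listed events will occur over 24 weeks. The documents give no event rates, so the following is illustration only. Assume each of 266 participants independently has probability p of at least one listed event. The expected number affected is 266p, and the chance of none is (1 − p)^266.

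| Assumed p | Expected participants | Chance of none |
|---|---|---|
| 0.5% | 1.3 | 26.4% |
| 1% | 2.7 | 6.9% |
| 2% | 5.3 | 0.5% |
| 5% | 13.3 | about 0.0001% |

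The sentence is therefore poorly founded over most of this range. It does not remove any event from the count, because listed events are recorded whatever was expected.

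**Means and individual worsening.** Assume that PSYRATS-AH change scores are normal with SD 11 (the article gives 11.0 only as a pooled SD, so using it for change is an assumption) and that the mean improvement is 3.8 to 8 points. The share scoring worse than baseline is Φ(−mean/SD):

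- mean improvement 3.8: Φ(−3.8/11) = Φ(−0.345) ≈ 37%
- mean improvement 8: Φ(−8/11) = Φ(−0.727) ≈ 23%

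This shows two things. A clear mean improvement can coexist with many participants scoring worse. And a table of anyone worse than baseline would be filled largely by ordinary variation, so it needs a margin.

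**The case against.** The strongest reply is that little is actually unmeasured.

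- Cybersickness has its own questionnaire in the arm where it can occur.
- The hospitalisation and the severe examples in item 11b are all on the list. Self-harm carries no severity threshold, and complaints are recorded too.
- Milder worsening would show on PSYRATS-AH total and distress, rated by blinded assessors, with assessment continued where possible after participants leave treatment.
- The expectation of no events can be read as referring to VR-related events only, in which case planning for hospitalised participants does not contradict it.
- How worsening is tabulated is commonly left to the analysis plan, which is not shown.

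Most of this stands, and it rules out stronger readings. A reader might infer that tolerability would look good by construction, or that the list was chosen to exclude the main harm. The documents support neither: no section says that a tolerability conclusion will rest on the event count alone, and nothing speaks to motive. A reader might also infer that cybersickness goes unmeasured or that only severe events count. The points above contradict both.

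Three things survive. First, the article says that it constitutes the full trial protocol (item 31c), and what is recorded as an adverse event is a protocol matter, so the definition in item 22 is the operative one. Second, even on the narrow reading, the expectation sits badly with the cybersickness sentence and with therapy-related deterioration in item 11b. Third, collecting scales is not the same as reporting harms from them. Nothing links them to the harms report, and item 18b lets a shortened interview favour primary and secondary outcomes, so SIDAS, SAPS and the sickness questionnaire are the measures more likely to be lost.

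**Conclusion.** The point holds as a gap in definition and cross-reference. Deterioration suspected to come from the intervention, when short of a listed event, is not counted as a harm, and the sickness results are not tied to harms reporting. The sentence expecting no events is unsupported and does not fit its surroundings. The consequence is confined to a tolerability statement based on the adverse-event count alone.

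The size cannot be given. A reader might assume deterioration rates, say 10% against 5%, and conclude that 133 × 0.10 ≈ 13 and 133 × 0.05 ≈ 7 participants would be missing. Those rates have no source in the documents, and some of these participants would be counted anyway through admission, self-harm or complaint.

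The conclusion rests on reading the list in item 22 as complete, which is how it is worded. The primary analysis and the sample size are not affected. This is an inexpensive improvement to safety reporting and is worth making.

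**What to change.** Reconcile items 11b and 22 and the exploratory outcomes section. The clinical handling in item 11b can stay as it is; only recording and reporting change.

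1. Delete the sentence expecting no adverse events. Define adverse event and serious adverse event, and use each consistently.
2. Record deterioration suspected to be caused by the intervention as an adverse event, and report the Simulator Sickness Questionnaire results in the harms section.
3. From the blinded week-12 assessments, report by arm the number assessed and the number whose PSYRATS-AH total worsened by more than a margin fixed before unblinding.

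The table in step 3 should carry the between-arm comparison. The item 11b cases should not: the only supervision the article describes is that of the trial therapists, so those cases would come mainly from the VRT arm. The contact registration in item 11a is no substitute either. It should capture admissions in both arms, but not reliably self-harm or violent incidents.

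The cost is protocol wording, slightly more logging and one table from data already planned. The harms table may look less favourable.
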